### Evaluating the impact of HHM on hypertension management and tobacco screening and cessation

2.7

HHM uses two outcome measures derived from Clinical Quality Measures (CQM) from the Centers for Medicare and Medicaid Services (CMS): CMS165v10 (controlling high blood pressure) and CMS138v11 (tobacco screening and cessation intervention) (Table 2). These measures represent the HHM intervention's impact at the WHC level. The measures will be treated as proportions, with the numerator being the number of patients that met the measurement criterion and the denominator being the number of eligible patients during the measurement period. To calculate these two measures, several data components will be collected monthly from each participating WHC throughout the study period from the baseline through the maintenance phase, a total of 35 months. For each monthly data collection, we will use a 12-month look-back period, meaning that each data point represents aggregate outcomes from the previous 12 months. In the end, one data point related to hypertension management and one data point related to tobacco cessation will be collected per WHC per month, both reflecting data from the preceding 12 months. The 12-month look-back period was selected to align with the definition of the outcome measures and was determined to be feasible given the natural limitations of the participating WHCs' electronic health records systems. EvidenceNow projects using coaching and similar QI interventions have previously documented challenges associated with using EHR data to enable the calculation of performance measures [[32], [33], [34]]. Descriptive statistics will be calculated for all measurements monthly across the study period, including means and standard deviations, and ranges, or counts and percentages, as appropriate.

**Table 2 tbl2:** Primary outcome measures and related data elements.

Measure	CMS165v10 [35]	CMS138v11 [20]
Measure Definition	Percent of patients, 18–85 years of age, who had a diagnosis of essential hypertension starting before and continuing into, or starting during the first 6 months of the measurement period, and whose most recent BP was adequately controlled (<140/90 mmHg) during the measurement period.	Percentage of patients aged 18 years and older who were screened for tobacco use one or more times during the measurement period AND who received tobacco cessation intervention during the measurement period if identified as a tobacco user.^a^

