Data Elements Collected Monthly from Electronic Health Records	1.The number of adults (18–85) who: had at least one visit to the health center during the measurement period; AND had at least one blood pressure measure recorded during the measurement period	
	2. The number of adults in (1) who have ever been diagnosed with hypertension	4.The number of adults in (1) who were screened for tobacco use during the measurement period
	3. The number of adults in (2) whose most recent systolic blood pressure measurement is ≤ 139 AND diastolic blood pressure measurement is ≤ 89	5. Number of adults in (4) who were identified as a tobacco user
		6. Number of adults in (5) who received a tobacco cessation intervention (including counseling and/or pharmacotherapy) during the measurement period.
Denominator	(2) Adults with hypertension	(1) Initial Population – rate 1
Numerator	(3) Controlled hypertension	(4) Adults who screened for tobacco use – rate 1

a Three rates are reported for CMS138v11: (1) Percentage of patients aged 18 years and older who were screened for tobacco use one or more times during the measurement period, (2) Percentage of patients aged 18 years and older who were identified as a tobacco user during the measurement period who received tobacco cessation intervention during the measurement period or in the six months prior to the measurement period, and (3) Percentage of patients aged 18 years and older who were screened for tobacco use one or more times during the measurement period AND who received tobacco cessation intervention during the measurement period or in the six months prior to the measurement period if identified as a tobacco user.

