#### Power and sample size

2.7.2

The pragmatic single-arm hybrid effectiveness-implementation study focuses on the comparison of WHC-level study outcomes between baseline and over the 12-month period of intervention (Fig. 2). The baseline WHC-level performance for CMS165V10 is estimated at 44 % and CMS138V11 is estimated at 20 % (tobacco screening), respectively, based on previously published studies [[43], [44], [45]]. We anticipate that a 15 % improvement in these measures over the 12-month period of intervention represents a meaningful improvement, which we believe is a conservative estimate based on previous studies [46,47]. For example, one study demonstrated that similar interventions to HHM have resulted in a 28.6 % improvement in CMS165v10, which is about twice more significant than our assumption [48]. Given the nature of the study outcomes, we performed power calculations for a two-sided paired *t*-test with an alpha level of 0.05. Specifically, the improvement is expected to be 0.15 with a pooled standard deviation of 0.16, and the power calculation results revealed that we would have at least 84 % power to detect the increase in CMS165V10 from 44 % to 59 % and in CMS138V11 from 20 % to 35 % from the 12 WHCs [49].

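### The tobacco primary outcome is defined as screening plus cessation support but computed and powered as screening alone, so a significant result would support only a claim about screening

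*Protocol article*

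**What the plan says.** All references are to the protocol article.

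- **Section 2.7, Table 2, definition.** CMS138v11 is the percentage of adults who were screened "AND who received tobacco cessation intervention during the measurement period if identified as a tobacco user". This is a composite. It matches rate 3 in footnote a, except that the footnote also counts support in the six months before the measurement period.
- **Table 2, denominator and numerator rows.** The denominator is "1) Initial Population – rate 1" and the numerator is "4) Adults who screened for tobacco use", also labelled rate 1. This is element (4) over element (1).
- **Table 2, data elements.** Element (5) counts tobacco users among those screened. Element (6) is "Number of adults in (5) who received a tobacco cessation intervention (including counseling and/or pharmacotherapy) during the measurement period". Neither enters the numerator shown.
- **Table 2, footnote a.** "Three rates are reported for CMS138v11", but none is named as primary.
- **Section 2.7, text.** "one data point related to tobacco cessation will be collected per WHC per month", so a single monthly value is described as concerning cessation.
- **Section 2.7.1.** The paired t-test is applied to CMS138v11 with no rate named, and p < 0.05 is to be read as effectiveness of the intervention.
- **Section 2.7.2.** The planned change is 20 % to 35 %. The baseline carries the label "tobacco screening), respectively, based on previously published studies".

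**The concern.** One label, CMS138v11, covers two different quantities in the primary analysis. The definition says that a tobacco user counts as a success only if screened and supported. The numerator row and the planning baseline count everyone who was screened, whether or not users received anything.

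Two things are at stake. The first is the claim. Section 2.7.1 turns a significant test into a statement that the intervention works, and the study's aim covers screening and cessation. A test of rate 1 says nothing about support among users. The second is the planning figure. The 84 % power belongs to the screening rate and does not carry over to the composite in the definition. In addition, while the rate is unnamed, it could be settled after the results are known.

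**Working it through.** **Inputs from the protocol article.** 12 WHCs, two-sided paired t-test, alpha 0.05, gain 0.15, standard deviation 0.16, stated power at least 84 %, screening 20 % to 35 % (section 2.7.2). WHC smoking rates run from 13 % to 59 %. The 11 reported rates in Table 3 sum to 326, so their mean is 326/11 = 29.6 %.

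**Assumed, because the article gives no figure.** The share c of users who receive support, the user share u among those screened (WHC smoking rates stand in for it), and a standard deviation of 0.16 for the composite as well.

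**Step 1: the plan's own power.** Noncentrality = (0.15/0.16) × √12 = 3.25 with 11 degrees of freedom. The noncentral t distribution gives power 0.840. The stated 84 % reproduces if 0.16 is the standard deviation of the paired differences. This is the power for element (4) over element (1).

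**Step 2: the three rates.** With s the screening rate:

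- Rate 1 = (4)/(1) = s
- Rate 2 = (6)/(5) = c
- Composite (rate 3, 12-month window) = ((4) − (5) + (6))/(1) = s × (1 − u(1 − c))

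Rate 1 contains neither u nor c. Its 15-point rise, and its 84 % power, are the same whatever happens to support among users.

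**Step 3: an illustration with unchanged support.** Take u = 0.30 and c = 0.30 at both times, so 1 − u(1 − c) = 1 − 0.30 × 0.70 = 0.79.

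| Rate | Before | After | Change |
|---|---|---|---|
| Rate 1 | 20.0 % | 35.0 % | +15.0 points |
| Rate 2 | 30.0 % | 30.0 % | 0 |
| Composite | 0.20 × 0.79 = 15.8 % | 0.35 × 0.79 = 27.65 % | +11.85 points |

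For the composite, the noncentrality is (0.1185/0.16) × √12 = 2.57 and power is about 65 %.

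**Step 4: the range.** With support constant, the composite gain is 0.15 × (1 − u(1 − c)).

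| User share u | Gain, c = 0.2 to 0.8 | Power at SD 0.16 |
|---|---|---|
| 0.13 | 0.134 to 0.146 | 75 % to 82 % |
| 0.30 | 0.114 to 0.141 | 61 % to 79 % |
| 0.59 | 0.079 to 0.132 | 35 % to 74 % |

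In every case the composite gain and its power are below the stated 0.15 and 84 %.

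**Step 5: does the composite isolate support?** No. In step 3 it rises 11.85 points with support unchanged. Only rate 2 stays at zero there.

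**The case against.** The strongest counter-argument is that the plan does fix the rate. The Table 2 rows and the power section agree on screening, against one composite definition, and screening is an explicit part of the aim. The rate 1 label on both rows may also mean that rows for rates 2 and 3 were lost when the table was read, so little should rest on their absence. The study calls itself exploratory and a pilot, and nothing would be lost irrecoverably.

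Much of this is fair. Rate 1 is a legitimate primary outcome if it is named as such. But the definition still says something else, and the screening label in section 2.7.2 does not depend on how the table was read. If rows for the other rates do exist, three rates compete for one tobacco primary outcome and the ambiguity remains.

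Four stronger readings are tempting, and the article does not support them.

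- **Rates 1 and 3 could give opposite conclusions.** This is not shown. In the illustration both rise. Even if support fell from 50 % to zero with 59 % users, the composite would go from 0.20 × 0.705 = 14.1 % to 0.35 × 0.41 = 14.35 %, which is near null but not reversed.
- **The cessation aim is wholly unexamined.** Elements (5) and (6) are collected, three rates are to be reported, and descriptive statistics are planned for all measurements. Support would be visible. It is just not in the primary test under rate 1.
- **Making the composite primary cures the problem.** It does not, by step 5.
- **The footnote's six-month clause carries baseline support into the post-intervention value.** The study's own definition and element (6) count only the measurement period, so this is an inconsistency in the footnote.

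**Conclusion.** The inconsistency is real and sits in the stated text: a composite definition, a screening-only numerator and denominator, a screening baseline for power, and a primary test with no rate named. Under rate 1, p < 0.05 supports a change in tobacco screening and nothing about support for users.

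The stated power is not an arithmetic error. It is 84 % for rate 1, on the reading that 0.16 is the standard deviation of paired differences. For the composite, the same screening change with constant support gives a smaller gain: 11.9 rather than 15.0 points in the illustration. Power is then about 35 % to 82 % over user shares of 13 % to 59 % and support of 20 % to 80 %. Those composite figures depend on assumed support levels, on clinic smoking rates standing in for the user share, and on an unchanged standard deviation. They show direction and rough size and are not a forecast. The contradiction itself needs none of these assumptions.

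It should be settled before outcome data are analysed, because it decides what the tobacco test can conclude.

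**What to change.** Name one primary tobacco rate and use it in Table 2, section 2.7, section 2.7.1 and section 2.7.2.

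- **If the composite is primary:** compute it as ((4) − (5) + (6))/(1), and restate its baseline, expected gain, standard deviation and power.
- **If rate 1 stays primary:** rewrite the Table 2 definition as screening alone, describe the monthly data point accordingly, and limit the effectiveness claim to tobacco screening. The power figure can stand.
- **In either case:** make rate 2, (6)/(5), a named secondary outcome with the same paired test, and base any cessation claim on it, since it alone isolates support among users.
- **Editorial:** bring the six-month clause in footnote a into line with the 12-month window in the definition and element (6).

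The cost is wording, plus new planning figures if the composite is chosen. Elements (1), (4), (5) and (6) are already collected monthly, so no new data are needed.

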#### Statistical analysis plan

2.7.1

The primary outcomes of interest analyzed are WHC-level CMS165 V10 and CMS138v11. Due to the outcomes of this study representing aggregate outcomes from the previous 12 months, we will use data collected from the first month of intervention (reflecting only baseline phase data) to compare with data collected in the first month after completion of the intervention (reflecting the 12-month intervention). This approach minimizes contamination from overlapping periods and ensures a clear comparison between the baseline and the 12-month intervention. In the main analysis, we will utilize a paired *t*-test to evaluate whether there is a significant improvement in the study outcomes between the baseline and the 12-month intervention [36]. Each WHC serves as its own control in the paired analysis, and the differences in study outcomes between the baseline and the 12-month intervention are assumed to follow normal distributions [37]. The paired *t*-test will test the null hypothesis that there are no significant differences in outcomes between two time points. A p-value of <0.05 will indicate a significant change in outcomes, implying the effectiveness of the intervention. If the normality assumption is violated, we will consider a non-parametric alternative, such as the Wilcoxon signed-rank test [38]. The paired *t*-test will test the null hypothesis that there are no significant differences in outcomes between two time points. A p-value of <0.05 will indicate a significant change in outcomes, referring to the effectiveness of the intervention.

We will conduct two sensitivity analyses to account for potentially underlying temporal trend in the study outcomes and to explore “time-on-treatment effect” by incorporating more data points collected before and after intervention and leveraging the time-on-treatment effect model proposed by Hughes et al. [39].$$\mu_{ij}=\mu +\mu_{i}+\beta_{j}+\theta \left(s_{ij}\right)\;X_{ij}$$where $\mu_{ij}$ represents the expectation of the outcome, $y_{ij}$, (e.g., CMS165v10) at WHC *i* at time point *j*; μ is an intercept term that denotes the grand mean of the outcome at baseline; the random intercepts, $\mu_{i}$, represents each cluster's unique baseline; the effect of time is modeled as a categorical variable, and its fixed effect is represented by $\beta_{j}$; $X_{ij}$ is the indicator of intervention phase for WHC i at time point j; $\theta \left(s_{ij}\right)$ is the intervention effect as a function of the exposure time in the intervention phase, with $s_{ij}$ indicating the exposure time of intervention for cluster i at time j. The model is further illustrated in the Supplementary Figure.

Given the nature of the data collection procedure in this study, we assume that the intervention effect would be gradually reflected by the outcome data collected over time (i.e., a linear time-on-treatment effect reflected by $\theta \left(s_{ij}\right)=\left(\theta *s\right)$ in the Sensitivity Analysis 1. In this scenario, *s* denotes the exposure time of the intervention for cluster i at time j, and the maximum number of periods that a cluster can be exposed under intervention is 12 months; θ is the monthly fractional effect for a WHC [39]. Further, we will add an indicator for the parent companies of WHCs (0 = Company A; 1 = Company B) in the model above to account for a difference in the outcome at baseline between the two companies.

In Sensitivity Analysis 2, we will explore post-intervention effects, using data collected at baseline, intervention, and 6 months post-intervention. In this analysis, we will assume a general time-on-treatment effect, instead of the linear effect to test different patterns of the intervention effect [39]. It is worth noting that in the Sensitivity Analysis 2 we plan to model the underlying time trend by assuming a linear effect based on existing literature and will examine this assumption using the data collected from the baseline [40,41]. These analyses will depend on model convergence and stability and aim to provide additional insights into the intervention's impact.

Given the study's small sample size, we will apply the Satterthwaite correction, which is recommended for mixed models to account for small sample size limitations, in both sensitivity analyses [42]. We will also perform model diagnostics using residual and quantile-quantile plots. All analyses will be performed using SAS (version 9.4, SAS Institute Inc, Cary, NC) and/or R (version 4.40; the R Foundation for Statistical Computing Platform).

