### Study design

2.3

The HHM study design is inspired by stepped-wedge, cluster-randomized trial but differs in key ways with its smaller sample size, exploratory nature, and pragmatic focus. It is best described as a pragmatic single-arm hybrid effectiveness-implementation study, emphasizing the implementation and testing of HHM in WHC's unique clinical setting and practical application [17]. Specifically, the intervention is administered and measured at the WHC level, and WHC-level aggregated data are retrieved from existing EHR registries. The first 10 months of the project are dedicated to logistic planning, interviews with WHC clinicians, and adaptation of HHM strategies. All WHCs begin in the baseline phase and then shift to the intervention phase at staggered time points. The baseline phase is the control condition, during which WHCs continue with their usual care for at least six months. The baseline phase begins in HHM's eleventh project month for all WHCs. The intervention phase, which lasts for 12 months, is when WHCs receive coaching on the HHM clinical interventions. Once the intervention phase is completed, each WHC will be moved to a maintenance phase, which lasts for at least six months. During such time, although WHCs will no longer receive any coaching, data collection will continue. Fig. 2 illustrates the study timeline for the participating WHCs. [NAME BLINDED FOR PEER REVIEW] Institutional Review Board (IRB) approved the HHM protocol and serves as the single IRB.

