### Randomization

2.4

We used stratified randomization based on WHCs' parent companies (i.e., Companies A and B) to ensure the balance of WHCs across treatment sequences. A total of 12 WHCs were selected, seven from Company A and five from Company B, determined by the companies’ capacity and willingness to participate. Within each company stratum, the timing of the implementation introduction was randomly allocated [29]. In an effort to minimize participation burdens on the Companies (i.e., company leaders participated in kick-off calls with the WHCs as they began the intervention), we alternated intervention start dates between WHCs from Companies A and B (starting with those with the smallest numbers) to balance rollout across the two companies over time. Company A was assigned to start first because it had more WHCs participating. All randomization was conducted in SAS (version 9.4, SAS Institute Inc, Cary, NC).

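### Both sensitivity models use overlapping 12-month values with only a WHC random intercept, so as written their standard errors are too small for most effects

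*Protocol article*

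**What the plan says.** Section 2.7 defines the data: "For each monthly data collection, we will use a 12-month look-back period, meaning that each data point represents aggregate outcomes from the previous 12 months". Values are collected "throughout the study period from the baseline through the maintenance phase, a total of 35 months", and "one data point related to hypertension management and one data point related to tobacco cessation will be collected per WHC per month".

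Section 2.7.1 recognises the overlap for the main analysis. It compares the value from the first month of intervention with the value from the first month after it, so the two windows do not overlap.

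The two sensitivity analyses are meant to allow for an underlying time trend and to explore the effect of time on treatment, "by incorporating more data points collected before and after intervention and leveraging the time-on-treatment effect model". The model equation contains an intercept, a random intercept per WHC, calendar time and an exposure-time effect. A company indicator is added.
- **Sensitivity Analysis 1 (SA1):** categorical calendar time and an exposure effect linear in months, up to 12.
- **Sensitivity Analysis 2 (SA2):** a linear calendar trend and a general exposure-time effect, with data to 6 months after the intervention.

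The only stated safeguard for inference is that "we will apply the Satterthwaite correction, which is recommended for mixed models to account for small sample size limitations, in both sensitivity analyses". Residual and quantile-quantile plots are planned, with no action tied to what they show.

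**The concern.** A random intercept implies the same correlation between any two months of one WHC. Overlapping windows produce something else: very high correlation between neighbouring months that fades to nothing once the windows no longer overlap. If that serial part is left out, the model counts slowly drifting values as many separate pieces of information. Satterthwaite changes the reference degrees of freedom. It does not change a standard error computed from the wrong residual covariance.

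The paired t-test is a before-after comparison with no adjustment for calendar time, so a secular improvement would pass as an intervention effect. The sensitivity models are the only planned check on that. If their intervals are much too narrow, they could falsely appear to corroborate a before-after difference that comes from the trend.

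**Working it through.** **1. The plan's own figure.** Section 2.7.2 states at least 84% power for the paired t-test. With n = 12, difference 0.15 and 0.16 read as the SD of the differences, the noncentrality is 0.15 / (0.16/√12) = 3.248. With 11 df and critical value 2.201, power is 0.840. The figure reproduces and concerns only the main analysis. The article gives no standard error or error rate for the sensitivity models.

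**2. Inputs.**
- Look-back of 12 months and a 35-month series (section 2.7).
- "A total of 12 WHCs were selected, seven from Company A and five from Company B".
- "The baseline phase is the control condition, during which WHCs continue with their usual care for at least six months", then 12 months of intervention and at least 6 of maintenance (section 2.3).
- Assumed, because Fig. 2 is not shown: one start per month in months 7 to 18. With 12 separate starts this fits, since 6 + 11 + 12 + 6 = 35.
- Baseline months then total 6 + 7 + … + 17 = 138. Adding 12 × 12 = 144 intervention months gives 282 WHC-months for SA1. A coding with 294 was also run.

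**3. Correlation from overlap.** For an equal-weight mean of 12 independent months, the correlation at lag k is max(0, 1 − k/12). At lag 1 it is 11/12 = 0.92, and at lag 12 it is 0.

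**4. Null simulation.** Values were 12-month rolling means of independent monthly noise plus a WHC intercept, with no intervention effect. The models were fitted by REML with a random intercept and independent residuals. Residual df stood in for Satterthwaite. A control with truly independent monthly values gave SE ratios of about 0.95 to 1.05 and rejection of about 4 to 7%, so the code behaves.

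| Quantity | Model SE / true SE | Null rejection at 5% |
|---|---|---|
| SA1 effect, 294 WHC-months | 0.31–0.33 | 51–54% |
| SA1 effect, 282 WHC-months | 0.042/0.138 = 0.30 | about 55% |
| SA2 average effect | 0.42–0.47 | 35–42% |
| SA2 month 12 or 18 | 0.45–0.49 | 33–38% |
| SA2 month 6 | 0.61–0.64 | 20–22% |
| SA2 month 1 | about 1.2 | 2–3% |
| SA2 joint test (18 df) | – | 17–19% |

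**5. Hand check.** If the model SE is r times the true SE, the rejection rate is about 2[1 − Φ(1.96 r)]. This gives 55% for r = 0.30, 41% for r = 0.42, 34% for r = 0.49 and 2% for r = 1.2, in line with the table.

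**6. Ranges.**
- With 10 df: SA1 45–48%, SA2 averages 30–36%. Fewer degrees of freedom help little.
- Autocorrelated underlying months (0.5 to 0.8): SA1 57–58%, SA2 averages 39–45%.
- Six steps of two WHCs: SA1 54%, SA2 averages 37–39%.
- Added independent monthly noise equal to the rolling SD: SA1 33%, SA2 averages 23–26%.
- Last-reading weights. CMS165v10 uses the most recent reading in the window, so recent months weigh more. With monthly visit probability p (assumed; the article gives none) and q = 1 − p, the lag-1 correlation is q(1 − q²²)/(1 − q²⁴). For p = 0.1, 0.2, 0.33 and 0.5 it is 0.88, 0.80, 0.67 and 0.50. The SA1 SE ratio is 0.34, 0.39, 0.49 and 0.60, and rejection is 50%, 44%, 34% and 24%.

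**7. Does the remedy work?** Permuting start order within company gave null rejection of 4.4 to 4.9% for SA1. Generalised least squares with correlation 1 − lag/12 gave 5.0% for SA1 and 5.0 to 5.6% for SA2 using residual df. With 11 df it gave 2.8% for SA1, which is conservative. These rates are for data that follow that covariance.

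**The case against.** **Independence is inferred.** The equation describes the mean of the outcome, and the article never says that residuals are independent. The supplementary figure is not shown, and a residual covariance might be left to a fuller plan. This stands as a limit on wording: the model as written specifies no residual correlation. It does not remove the point. The section sets out the random effect, the time coding, the company term and the small-sample correction, and the overlap is known from the design.

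**The main result is safe.** A reader might infer that the trial's primary conclusion is compromised. It is not, on this ground. The p < 0.05 effectiveness rule belongs to the paired t-test, which uses non-overlapping windows. The sensitivity analyses are exploratory, carry no decision threshold and depend on convergence. This stands, and it lowers the severity.

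**The headline sizes do not cover both models.** It is tempting to say that standard errors are one third of the truth and that a null is significant half the time in both. That holds for SA1 under equal weights. SA2 is less affected, and its first-month standard error is, if anything, too large.

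**A positive claim is not the default.** The rejections are two-sided. In an SA1 null run with 56% rejection, 28% were significant in the favourable direction. That is still far above the 2.5% expected in one direction.

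**Conclusion.** The point holds in this form. As written, both sensitivity models leave the 12-month overlap out of the residual covariance, and Satterthwaite df does not make up for it.
- **SA1:** standard error about 0.3 of the true one and about 50% false positives at nominal 5%. The range is about 25 to 58% across assumptions on visit frequency, autocorrelation and extra noise.
- **SA2:** standard errors about 0.4 to 0.5 of the true ones for average and late effects, with about 33 to 42% false positives (23 to 26% for averages with added noise). The joint test rejects about 17 to 19%. The first-month effect is not anti-conservative.

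The exact sizes rest on an assumed start schedule and assumed monthly noise. The direction for the SA1 effect and for SA2 average and late effects was the same in every setting tried. Severity: should-fix, because the harm is false reassurance about calendar trend and the paired t-test itself is untouched.

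**What to change.** Keep both mean models and change the inference.

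1. **P-values:** use a permutation test that re-draws start order within Company A and within Company B, following the allocation as it was carried out. There are 7! × 5! = 604,800 possible orders, ample for a p-value.
2. **SA1 interval:** obtain it by inverting the same test, since SA1 has a single effect.
3. **SA2 exposure curve:** fit a within-WHC serial residual covariance that allows for the 12-month overlap, for example a banded Toeplitz form, with small-sample df. Use the triangular form 1 − lag/12 only if the measure behaves as an equal-weight rolling mean. The last-reading rule of CMS165v10 gives reason to doubt that.
4. **Reporting:** do not report the independent-residual standard errors.

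The cost is wording, a little more code and wider intervals. No new data are needed.

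### Sensitivity Analysis 2 assumes a straight-line calendar trend, and its only named linearity check uses baseline months that end before any post-coaching reading begins

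*Protocol article*

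**What the plan says.** Section 2.7.1 of the protocol article first sets out a mixed model in which "the effect of time is modeled as a categorical variable, and its fixed effect is represented by" a separate coefficient for each time point. Sensitivity Analysis 2 then changes two parts of it.

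- **Exposure time:** "we will assume a general time-on-treatment effect, instead of the linear effect to test different patterns of the intervention effect".
- **Calendar time:** "we plan to model the underlying time trend by assuming a linear effect based on existing literature and will examine this assumption using the data". The data meant are baseline data: the authors "will examine this assumption using the data collected from the baseline".

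This analysis uses baseline, intervention and six months of post-intervention data. The only other diagnostics named for it are general: "We will also perform model diagnostics using residual and quantile-quantile plots". Both sensitivity analyses are described as dependent on convergence and stability.

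Two design facts matter. Section 2.3 says "All WHCs begin in the baseline phase and then shift to the intervention phase at staggered time points", so no WHC stays untreated. Section 2.7 says data are collected "throughout the study period from the baseline through the maintenance phase, a total of 35 months".

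**The concern.** In Sensitivity Analysis 2 the calendar term can absorb only straight-line change shared by all WHCs. The exposure effect is left free, so a shared bend or step (a guideline, EHR or company-wide policy change, say) can load onto it.

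The named safeguard is to examine linearity in baseline data. That helps only if baseline data exist in the months where the assumption does its work. Sensitivity Analysis 2 is the only planned quantitative analysis of what happens after coaching stops, and the main paired t-test has no control for calendar time. A shared change late in the study could therefore be read as a lasting HHM effect, or could conceal one, after the linearity check had been passed.

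**Working it through.** **The article's own figure.** The article gives no number for Sensitivity Analysis 2. Its power figure belongs to the main paired t-test and reproduces: noncentrality 0.15/0.16 × √12 = 3.25, 11 df, two-sided 0.05, power 0.840 (stated: at least 84%).

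**Where baseline data end.** Section 2.3 gives at least 6 baseline months, 12 intervention months and at least 6 maintenance months. Section 2.7 gives 35 data months.
- Latest possible start: 35 − 12 − 6 + 1 = month 18, so the last baseline reading is in month 17.
- Earliest possible start: month 7, so the first post-coaching reading is in month 7 + 12 = 19.

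These bounds do not need Fig. 2, which is not shown. They take the 35 months as one window common to all WHCs. Section 2.7.1 treats the first intervention-month reading as baseline data; counting it extends the check only to month 18.

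**Assumed layout for size.** 35 − 6 − 12 − 6 = 11 months of stagger, so one start per month in months 7 to 18. This gives 354 WHC-months, 150 of them in months 18 to 35. Of those 150, none is baseline.

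**Bias.** Fitted model: y_ij = μ + μ_i + β·j + θ(s_ij) + e_ij, with 18 free exposure months. With a true HHM effect of zero and a shared change f_j, the expected estimate is (X′X)⁻¹X′f. Results in points for an illustrative 5-point change (they scale in proportion):

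| Shared change | Exposure month 12 | Mean of months 13–18 | Month 18 |
|---|---|---|---|
| Look-back ramp, months 18–29 | +1.9 | +2.8 | +3.3 |
| Look-back ramp, months 24–35 | +0.2 | +1.1 | +2.0 |
| Rise over months 1–17, then plateau | −1.3 | −2.2 | −2.9 |
| Purely linear | 0.0 | 0.0 | 0.0 |

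With starts in pairs or in three groups of four, the month-18 shares of the 5-point change are 63% and 55% for the first row (3.2 and 2.8 points) and 35% and 32% for the second (1.8 and 1.6 points). Random WHC intercepts (ICC 0.5 or 0.9) with a company indicator move the results by at most about 0.2 points.

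**Categorical months.** Replacing β·j with one effect per month gives a full-rank model (64 of 64 parameters) and a false effect of 0.0 in every scenario. It is identifiable because, within one calendar month, WHCs are at different exposure times.

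**False-positive rate at exposure month 18.** Case: ramp from month 17, independent residuals, bias about 3.3 to 3.4 points. The standard error is σ√[(X′X)⁻¹] = 0.59σ for the linear version and 0.74σ for the categorical one (ratio 1.26).
- σ = 2, 3, 4 points: simulated rejection 77%, 44%, 28% (normal approximation 83%, 49%, 31%).
- σ = 8: 3.4/(0.59 × 8) = 0.72, rejection about 11%.
- σ = 11: 3.4/(0.59 × 11) = 0.52, rejection about 8%.
- Categorical months: about 4.4% in simulation.

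If the 12-month overlap of readings is modelled, the linear bias for a ramp from month 18 is 4.1 to 4.3 points and the categorical standard error is about 1.76 times the linear one.

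**The case against.** The strongest defence is that a linear trend is a reasonable bias–variance choice in an analysis the authors label exploratory and conditional on convergence. They disclose the assumption, cite literature for it and plan a check.

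Much of this stands. With overlap modelled, σ = 4 and a 5-point change, the linear version's root mean squared error is √(4.1² + 3.4²) = 5.3 points, against 5.9 for the categorical version. Full rank is not stability: month 35 is seen in one WHC and month 34 in two. At σ = 2 the categorical version is clearly better, so the ranking turns on an SD the article does not state. Its only variability figure is 0.16; if that were entirely reading-level noise in a paired difference, it would imply 0.16/√2 = 0.11 per reading, an upper-end value.

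Other planned outputs also look beyond baseline. Residual plots could show misfit, and monthly descriptive statistics could show a large common change. They are weak here. Under the ramp from month 18 the largest mean monthly residual is about 0.9 points, because the free exposure effects absorb much of the change. A descriptive rise after month 17 cannot be separated from HHM when every WHC is already exposed. The linear calendar trend is attached to Sensitivity Analysis 2 alone, so Sensitivity Analysis 1 gives a cross-check, but only up to exposure month 12.

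A reader might infer that any late shared change would be credited to HHM in full. It would not: in the late-change scenarios under monthly starts, including abrupt steps, 4% to 83% reaches exposure month 12 and 22% to 78% reaches months 13–18. The rest goes to the slope and residuals.

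**Conclusion.** The point holds as a limited one. The named linearity check cannot see the months in which Sensitivity Analysis 2 estimates post-coaching effects, and a shared non-linear change there would be partly attributed to HHM or could mask an effect. For a 5-point change entering through the look-back, the distortion at exposure month 18 is about 3.3 points (from month 18) or 2.0 (from month 24), and it turns negative if a rising trend levels off.

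That baseline and post-coaching months do not overlap follows from the stated phase lengths. The sizes rest on an inferred stagger and an illustrative change.

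Two stronger readings are not supported. First, a false-positive rate near 77% is not a property of the plan: it needs a 2-point residual SD, and the rate is about 8% to 11% at 8 to 11 points. Second, the main effectiveness conclusion is not affected, since it rests on the paired t-test. This is a cheap improvement to an exploratory analysis.

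**What to change.** Keep the linear-trend fit in Sensitivity Analysis 2. Beside it, fit and report the categorical-time version already defined in section 2.7.1, with the same general time-on-treatment effect. Replace the baseline-only check with a comparison of linear and categorical month over all 35 data months. Describe a post-intervention effect as robust only if the two versions agree, and state beforehand what counts as agreement. Judge that on the difference between the two estimates, not on whether both reach significance.

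The cost is a sentence or two of analysis wording and one extra fit, with no new data. The categorical estimate is less precise: its standard error at exposure month 18 is about 1.3 times larger with independent residuals and about 1.8 times larger when look-back overlap is modelled. It therefore serves as a robustness comparison and should not replace the linear version.
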